## Abstract

**Background::**

Although ultrasonography (US) is widely recommended for HCC surveillance, its limited sensitivity for early-stage HCC remains a concern. Gadoxetic acid–enhanced abbreviated MRI (HBP-AMRI) has demonstrated high diagnostic performance; however, its role in routine surveillance settings remains uncertain due to limited prospective comparative evidence. The AMRIUS study (Abbreviated MRI using gadoxetic acid versus Ultrasonography for Surveillance of early-stage HCC in high-risk patients) aims to prospectively compare the effectiveness of HBP-AMRI and US for HCC surveillance in high-risk patients with cirrhosis.

**Methods::**

AMRIUS is a randomized controlled trial (RCT) enrolling 806 high-risk patients with cirrhosis, randomly assigned (1:1) to undergo either biannual HBP-AMRI or US for 2 surveillance rounds. The primary endpoint is the detection rate of early-stage HCC [Barcelona Clinic Liver Cancer (BCLC) stage 0 or A]. Secondary endpoints include false referral rate of BCLC 0 or A HCC, detection and false referral rates for BCLC stage 0 and all-stage HCC, BCLC stage distribution at initial HCC diagnosis, and the rate of curative treatment. Structured imaging protocols and quality assessments will be implemented.

**Discussion::**

AMRIUS is the first RCT designed to provide high-level evidence comparing HBP-AMRI and US for HCC surveillance. Its findings are expected to inform future guidelines and support risk-adapted strategies that prioritize early detection and curative treatment eligibility, particularly for patients likely to benefit from high-sensitivity imaging.

**Trial Registration::**

Registered at Clinical Research Information Service on May 22, 2022 (KCT0007417) and ClinicalTrials.gov on March 9, 2024 (NCT06312826). Participant recruitment began on August 26, 2022. Follow-up is ongoing.

## INTRODUCTION

HCC is the sixth most common cancer and the third leading cause of cancer-related deaths worldwide.^1^ To improve patient outcomes, regular surveillance aimed at detecting early-stage HCC is recommended in at-risk populations, as early detection allows for timely curative treatment. Ultrasonography (US) is recommended as the primary surveillance modality in major clinical guidelines^2^,^3^,^4^,^5^; however, it has limited sensitivity for detecting early-stage HCC in high-risk individuals.^6^,^7^,^8^,^9^ A meta-analysis reported that the pooled sensitivity of US alone for detecting early-stage HCC in patients with cirrhosis was 47%,^6^ and prospective have shown a wide range of sensitivities, from 25.6% to 62.5%.^10^,^11^,^12^,^13^,^14^ Moreover, US performance varies considerably depending on factors such as imaging protocols, equipment quality, patient body habitus, liver morphology, and the operator’s level of expertise.^15^,^16^

To overcome these limitations, alternative imaging approaches are being explored for HCC surveillance in high-risk populations.^17^ Among these, gadoxetic acid–enhanced MRI has shown excellent performance in detecting HCC,^12^ primarily through hepatobiliary phase (HBP) imaging acquired 15–20 minutes after the intravenous injection of gadoxetic acid. This phase enhances lesion-to-liver contrast by exploiting hepatocyte-specific uptake of gadoxetic acid, facilitating early detection of small HCCs.^17^,^18^,^19^ However, the widespread application of full MRI for surveillance is limited by high cost, long scan time, and resource constraints. Abbreviated MRI using HBP imaging (HBP-AMRI) has demonstrated excellent diagnostic performance while reducing scan time by omitting dynamic contrast-enhanced sequences. Retrospective studies have consistently reported high sensitivity of HBP-AMRI for detecting HCC, ranging from 82.6% to 92.0%, and specificity ranging from 91.0% to 93.2%.^20^,^21^,^22^,^23^,^24^,^25^ However, these findings may be affected by selection bias, as the studies were primarily conducted in retrospective diagnostic contexts with a high HCC prevalence (14.9%–35.6%) and typically employed single-session AMRI rather than repeated imaging over time, which may limit their applicability to true surveillance settings. In addition, several studies used MRI as the reference standard,^21^,^22^,^23^,^25^ with both the simulated AMRI and the reference MRI derived from the same imaging session, introducing a lack of independence between the index test and the reference standard.

While HBP-AMRI is promising, robust comparative evidence against US in a surveillance setting is lacking. Prior studies employing single-arm or intraindividual designs^12^,^14^,^24^ may have underestimated the performance of US, as surveillance was often discontinued when MRI detected HCC earlier than US. This early termination limits direct temporal comparison between the 2 modalities. To address this limitation and provide high-quality evidence on their comparative effectiveness in HCC surveillance, we initiated a prospective, randomized controlled trial (RCT) to compare biannual US and biannual HBP-AMRI in high-risk patients with cirrhosis.

## METHODS

### Study design

The current trial [Abbreviated MRI using gadoxetic acid versus Ultrasonography for Surveillance of early-stage HCC in patients at high risk (AMRIUS)] is a prospective, single-center, open-label RCT designed to compare the efficacy of biannual HBP-AMRI and biannual US for the surveillance of HCC in high-risk patients with cirrhosis. The trial is being conducted at Asan Medical Center, a tertiary academic hospital in the Republic of Korea, which has 2432 beds and performs over 3000 liver imaging surveillance examinations annually, ensuring procedural consistency and technical expertise.

Participants meeting the eligibility criteria are randomly assigned in a 1:1 ratio to undergo either HBP-AMRI or US every 6 months during 2 consecutive surveillance rounds. The trial has been registered at ClinicalTrials.gov (NCT06312826) and in the Clinical Research Information Service of South Korea (KCT0007417). Participant recruitment began on August 26, 2022. Follow-up for primary and secondary endpoints is ongoing.

### Ethics approval and informed consent

This study was approved by the Institutional Review Board (Asan Medical Center; IRB number: 2022-0661). The trial is being conducted in accordance with the Declaration of Helsinki and Good Clinical Practice guidelines. Any modifications to the protocol will be implemented only after Institutional Review Board approval and notification to all participating investigators. Written informed consent will be obtained from all participating patients.

### Eligibility criteria

#### Inclusion criteria

Adults aged ≥20 years.Diagnosis of liver cirrhosis based on at least 1 of the following:Histological confirmation via liver biopsy, orRadiologic evidence of cirrhosis and portal hypertension, defined as typical imaging features of liver cirrhosis on radiologic examination with liver stiffness ≥12 kPa on transient elastography or the presence of esophageal or gastric varices.High risk for HCC (estimated annual risk >5%), defined as a risk index ≥2.33:Risk index=1.41 (if age ≥50 y) + 1.65 (if prothrombin activity ≤75%) + 0.92 (if platelet count ≤100 × 10^3^/μL) + 0.74 (if positive for anti-HCV or HBsAg).^26^
Eastern Cooperative Oncology Group performance status 0–2.No history or current evidence of HCC within 6 months prior to enrollment.Willing and able to provide written informed consent and comply with study procedures.

#### Exclusion criteria

Presence of an active or suspected cancer, or a history of treated malignancy with a risk of recurrence ≥20% within 2 years.Significant comorbidity with an expected survival of <3 years.Estimated glomerular filtration rate <30 mL/min/1.73 m^2^.Child–Pugh class C.Conditions precluding application of the Liver Imaging Reporting and Data System (LI-RADS) (eg, Budd–Chiari syndrome or other hepatic vascular disorders).Contraindications to MRI (eg, pacemakers, severe claustrophobia, pregnancy).Any condition deemed by the investigators to interfere with study participation or protocol adherence.

### Sample size

The sample size was calculated based on a 2-sided test for comparing 2 independent proportions, with the primary endpoint being the detection rate of early-stage HCC. Based on prior prospective studies in real-world surveillance settings,^12^,^13^,^14^ we assumed a cumulative prevalence of very early or early-stage HCC of 8% during the study period. The sensitivity of HBP-AMRI was estimated at 90%, and that of US at 35%, reflecting the range observed in surveillance cohorts of patients with cirrhosis.^12^,^13^,^14^ Accordingly, we assumed detection rates of 7.2% for HBP-AMRI and 2.8% for US. To detect a statistically significant difference in detection rates between the 2 modalities, with 80% power and a 2-sided alpha of 0.05, and accounting for an anticipated 5% dropout rate, the total required sample size is 806 participants (403 per arm).

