**FIGURE 1 F1:**
[figure not shown]
Participant flow. Abbreviations: HBP-AMRI, hepatobiliary phase-abbreviated magnetic resonance imaging; LR, Liver Imaging Reporting and Data System category; US, ultrasonography.

If a lesion is detected and considered potentially malignant based on predefined radiologic criteria (see *Imaging Evaluation* section below), a confirmatory imaging test will be conducted. Participants with no suspicious findings will proceed to the second surveillance round at the scheduled interval. Following completion of the second surveillance round, all participants will enter a 6-month observation period, during which delayed HCC diagnosis and clinical outcomes will be assessed. If a “positive” lesion is ultimately determined to be a false-positive following the confirmatory test, the participant will return to their assigned surveillance schedule.

Dropout will be defined as: (1) withdrawal of consent or determination by the investigators that the participant is unable to adhere to the protocol; (2) liver transplantation without prior HCC diagnosis, (3) diagnosis of extrahepatic malignancy during the study period, or (4) failure to complete one or more consecutive scheduled surveillance visits. To minimize dropouts, participants will receive up to 2 reminders per visit (3 d and 1 d in advance) via phone call or text message. In addition, staff will offer flexible scheduling support and follow-up if participants miss or need to reschedule an appointment.

Peripheral blood samples will be collected at the screening visit and at each surveillance visit for all enrolled participants following approved protocols. Serum levels of alpha-fetoprotein and protein induced by vitamin K absence-II will be measured at each visit. Stored samples may be used in future ancillary studies. Written informed consent will be obtained from all enrolled participants for specimen collection and future use.

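### The stated 80% power rests on a 2.8% US detection rate built from one sensitivity that the protocol itself says may be too low, with no allowance shown for the second US look

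*Protocol article*

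**What the plan says.** The Sample size section of the protocol article builds its effect size in one step. On prevalence: "we assumed a cumulative prevalence of very early or early-stage HCC of 8% during the study period". On accuracy: "The sensitivity of HBP-AMRI was estimated at 90%, and that of US at 35%, reflecting the range observed in surveillance cohorts". The products follow: "we assumed detection rates of 7.2% for HBP-AMRI and 2.8% for US". The trial is then sized "with 80% power and a 2-sided alpha of 0.05", with 5% dropout, at 806 participants (403 per arm). Both inputs are credited to references 12, 13 and 14. The section does not say when the study period ends, or whether the sensitivities refer to one examination or to a programme of examinations.

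Other sections bear on these inputs:

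- **Participant flow.** Round 1 takes place about 6 months after the last clear imaging study, and round 2 follows 6 months later. A participant with nothing suspicious at round 1 is tested again at round 2. After that, "all participants will enter a 6-month observation period, during which delayed HCC diagnosis and clinical outcomes will be assessed". No surveillance test is described for that period.
- **Outcomes.** The numerator of the primary endpoint counts only patients whose early-stage HCC was found by the assigned modality.
- **Introduction.** The single-arm and intraindividual designs of references 12, 14 and 24 are said to have possibly underestimated US, because surveillance was often stopped when MRI found the tumour first. The Discussion gives the same bias as the reason for randomizing.
- **Statistical analysis.** Detection rates will be compared with the Fisher exact test.

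**The concern.** The protocol criticizes earlier studies for not letting US find tumours later, and it randomizes in order to allow this. Its power calculation nevertheless takes the US sensitivity partly from those studies and applies it once.

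A second look helps the less sensitive test far more. US misses 65% of tumours at a look and HBP-AMRI misses 10%, so retesting round-1 misses narrows the planned difference. The bias named in the Introduction and the unmodelled second look therefore both make the planned contrast look larger than it may be.

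The stake is interpretation. If the two-round US rate is above 2.8%, a non-significant result would be read against a power of 80% that the trial did not have.

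**Working it through.** **1. Reproduce the plan.** Inputs from the Sample size section: 8%, 90%, 35%, two-sided alpha 0.05, power 80%, dropout 5%.

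- Rates: 0.08 × 0.90 = 7.2%; 0.08 × 0.35 = 2.8%.
- Unpooled formula: n = (1.960 + 0.842)² × (0.072 × 0.928 + 0.028 × 0.972) / 0.044² = 381.2, so 382 per arm.
- Dropout: 382 / 0.95 = 402.1, so 403 per arm and 806 in total. This matches exactly.
- Power at 382 per arm: 80% by the z test and 77% by the planned Fisher test.

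**2. Add the second look.** Let s be the sensitivity at one look. Let f1 be the share of the 8% detectable at round 1 and f2 the share first detectable at round 2; the remainder arises after round 2. Let q be the fraction of the independent second-look gain that is realized. It falls below 1 if misses are correlated between rounds or if a missed tumour is no longer BCLC 0 or A at round 2. Then

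rate = 8% × [f1 × (s + (1 − s) × q × s) + f2 × s].

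For a tumour present at both rounds with q = 1, US rises from 35% to 0.35 + 0.65 × 0.35 = 57.8%, and HBP-AMRI from 90% to 0.90 + 0.10 × 0.90 = 99%.

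With f1 = f2 = 0.5 and none after round 2:

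- q = 0.5: US = 8% × (0.5 × 0.46375 + 0.5 × 0.35) = 3.26%; HBP-AMRI = 8% × (0.5 × 0.945 + 0.5 × 0.90) = 7.38%.
- q = 1: US = 8% × (0.5 × 0.5775 + 0.5 × 0.35) = 3.71%; HBP-AMRI = 8% × (0.5 × 0.99 + 0.5 × 0.90) = 7.56%.

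**3. Add the observation period (conditional).** From the last clear image, round 2 falls at about 12 months and the study ends at about 18 months. With even accrual, one third of the 8% would arise after round 2, where no assigned test can find it (f1 = f2 = 1/3).

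- q = 0: 4.80% v 1.87%.
- q = 1: US = 8% × (0.5775 + 0.35) / 3 = 2.47%; HBP-AMRI = 8% × (0.99 + 0.90) / 3 = 5.04%.

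**4. Power at 382 evaluable per arm.** The z power is Φ{(|p1 − p2|√n − 1.960√[2p̄(1 − p̄)]) / √[p1(1 − p1) + p2(1 − p2)]}, where p̄ is the mean of the two rates. The Fisher power is exact.

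| Scenario | HBP-AMRI | US | z | Fisher |
|---|---|---|---|---|
| As planned | 7.20% | 2.80% | 80% | 77% |
| Half second-look gain | 7.38% | 3.26% | 72% | 68% |
| Full second-look gain | 7.56% | 3.71% | 64% | 59% |
| One third of cases after round 2, no gain | 4.80% | 1.87% | 62% | 56% |
| One third after round 2, full gain | 5.04% | 2.47% | 46% | 40% |

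The shares f1 and f2 and the fraction q are assumptions; the document gives none of them.

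**The case against.** The strongest reply is that the Sample size section never calls 35% and 90% per-examination values. It ties them to surveillance cohorts. If they are programme values over the same cases as the 8%, then prevalence times sensitivity is the right product and power stays at 80%. This stands, and the sources needed to settle it are not available here. It does not remove the point: even a programme-level 35% taken from references 12 and 14 carries the bias that the Introduction describes. As an illustration, the Introduction's pooled US sensitivity of 47% gives 8% × 0.47 = 3.76% against 7.2%, and a z power of 55%. The same paragraph also reports values below 35%, so power could move either way.

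A reader might take the Introduction's remark that studies "typically employed single-session AMRI rather than repeated imaging over time" as proof that the inputs are one-examination values. It is not. That remark concerns the retrospective studies, references 20 to 25, and not references 12 to 14.

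A reader might also infer from the entry criterion, "High risk for HCC (estimated annual risk >5%), defined as a risk index ≥2.33", that the 8% must include the observation period. With a constant hazard, 8% over 18 months needs −ln(0.92) / 1.5 = 5.6% a year, and 8% by round 2 needs −ln(0.92) = 8.3% a year. Both exceed 5%, which is only a floor, so the criterion does not decide the window. Delayed diagnoses during observation may also be tumours that were present and missed at round 2; those belong in the 8% and are already counted as misses. Tumours carried into round 1 from an earlier false-negative image would also shift cases towards the tested rounds.

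The full second-look gain is also generous. The Introduction attributes US performance partly to body habitus and liver morphology, which persist between rounds, so misses are likely to be correlated.

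**Conclusion.** The point holds in a conditional form. The arithmetic of 806 is correct for 7.2% v 2.8%. What is not supported is a single, unqualified 80%. The US rate relies on a sensitivity that the protocol itself considers possibly too low, and the calculation shows no allowance for the second US look in its own schedule.

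Unless 35% is already a two-round programme value free of that bias, power at 382 per arm is about 72% (Fisher 68%) with half the second-look gain and 64% (59%) with the full gain, assuming that half the cases are present at round 1. The lower figure of about 46% (40%) needs more: that the 8% includes cases first arising after round 2, that the sensitivities do not already count them as misses, that accrual is even, and that the full second-look gain is realized.

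A reader might infer that the trial is shown to be underpowered or that the sample size is miscalculated. The document supports neither, because it fixes neither the window of the 8% nor the unit of the sensitivities.

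**What to change.** Rewrite the sample-size paragraph so that it:

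1. states the window of the 8%, in particular whether it ends at round 2 or includes the observation period, and the annual risk that this implies;
2. states whether 35% and 90% are per-examination or two-round programme values, and how the bias named in the Introduction was handled for the 35%;
3. derives both detection rates over two rounds, with the shares of cases at each round and the assumed second-look gain written out;
4. replaces the single 80% with power at 806 over a range of US detection rates on both sides of 2.8%, including power for the planned Fisher test (about 77% at the planned rates with 382 per arm).

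If the inputs were meant as programme values up to round 2, saying so and justifying the 35% is enough for items 1 to 3.

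The cost is one paragraph of recalculation and probably a less favourable power statement. Enrolment, endpoint and test do not change. Follow-up is still under way, so the restatement is most credible if made before results are known.

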In contrast to prior intraindividual comparison studies of AMRI and US^12^,^14^,^24^ and ongoing prospective studies of HBP-AMRI and US (NCT04539717, NCT04288323), the AMRIUS trial is a randomized study designed to avoid bias caused by the higher sensitivity of MRI, which can lead to earlier detection of lesions that might have otherwise been detected later by US, thereby underestimating the performance of US. The recently published MIRACLE trial^34^ compared non-contrast AMRI with US in a randomized setting, reporting that the non-contrast MRI group detected tumors at earlier BCLC stages (*p*=0.01) and had a lower false-positive referral rate (*p*<0.001). However, the study failed to find a difference in early-stage detection rates and included an unstratified population with cirrhosis, limiting its applicability to risk-stratified surveillance. AMRIUS specifically targets high-risk patients and employs HBP imaging with gadoxetic acid, providing hepatocyte-specific contrast enhancement and excellent sensitivity for early-stage HCC. By integrating risk stratification with a contrast-enhanced abbreviated protocol, AMRIUS seeks to provide more robust evidence for optimizing surveillance strategies. Comparison of results from AMRIUS with those of other ongoing RCTs comparing different types of AMRI and US—such as non-contrast AMRI versus US (NCT05095714, NCT05429190) and dynamic contrast-enhanced AMRI versus US (NCT05486572)—is also anticipated.

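### The 80% power depends on an unadjusted US sensitivity of 35%, drawn partly from studies that the protocol says may understate US; across the protocol's own US range, power runs from 93% to 25%

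*Protocol article*

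**What the plan says.** The Sample size section of the protocol article sizes the trial as follows: "The sample size was calculated based on a 2-sided test for comparing 2 independent proportions". It sets the burden of disease first: "we assumed a cumulative prevalence of very early or early-stage HCC of 8% during the study period". It then sets the two sensitivities: "The sensitivity of HBP-AMRI was estimated at 90%, and that of US at 35%, reflecting the range observed in surveillance cohorts of patients with cirrhosis". The prevalence and the sensitivities are all cited to references 12, 13 and 14. Multiplying them out, "we assumed detection rates of 7.2% for HBP-AMRI and 2.8% for US". The target is stated "with 80% power and a 2-sided alpha of 0.05", and after 5% dropout the total is 806, or 403 per arm. No other power figure is given.

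Three other places bear on the 35%:

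- The Introduction cites a meta-analysis in which "the pooled sensitivity of US alone for detecting early-stage HCC in patients with cirrhosis was 47" per cent. It gives a range of 25.6% to 62.5% for prospective studies (references 10 to 14).
- The Introduction later says that single-arm or intraindividual studies (references 12, 14 and 24) "may have underestimated the performance of US, as surveillance was often discontinued when MRI detected HCC earlier than US".
- The Discussion returns to references 12, 14 and 24. It says AMRIUS is randomised to avoid a bias from MRI's higher sensitivity, "which can lead to earlier detection of lesions that might have otherwise been detected later by US, thereby underestimating the performance of US".

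The Statistical analysis section names the Fisher exact test for detection rates.

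**The concern.** The endpoint is a binary detection rate, so the US rate fixes both the assumed difference and part of the variance. Two of the three sources cited for it belong to the group that the protocol describes as possibly unfair to US. In AMRIUS, MRI findings do not end surveillance in the US arm. A tumour that US misses at the first round can still be found at the second, and it counts if it is still BCLC 0 or A. The trial is therefore meant to remove a bias that its planning rate may carry, and the Sample size section does not mention this.

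The direction is clear. If 35% is too low for a randomised two-round comparison, US will detect more than 2.8%, the true difference will be smaller than 4.4 percentage points (7.2% minus 2.8%), and power will be below 80%. What is at stake is how a non-significant primary result is read: it could be taken to mean that HBP-AMRI has no advantage when the trial had limited power to show one.

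**Working it through.** **Inputs.** From Sample size: prevalence 8%, HBP-AMRI sensitivity 90%, US sensitivity 35%, two-sided alpha 0.05, power 80%, dropout 5%. From the Introduction: US sensitivities of 47% (pooled), 25.6% and 62.5% (prospective extremes). The 40% value is an added intermediate point. From Statistical analysis: Fisher exact test.

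**Step 1. Reproduce the printed size.**

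Detection rates: 0.08 × 0.90 = 7.2% and 0.08 × 0.35 = 2.8%.

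n per arm = (1.960 + 0.842)² × (0.072 × 0.928 + 0.028 × 0.972) / 0.044² = 381.2, rounded up to 382.

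382 / 0.95 = 402.1, rounded up to 403 per arm, 806 in total. This is the printed figure, so the arithmetic is right for its inputs and the formula is the unpooled normal approximation.

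**Step 2. Vary only the US sensitivity.**

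Let p be the US rate, 0.08 × sensitivity. With n = 382 per arm:

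power = Φ( (0.072 − p) / √[(0.072 × 0.928 + p(1 − p)) / 382] − 1.960 )

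At 47%, for example: p = 3.76%, difference 0.0344, standard error 0.01642, ratio 2.095, and Φ(0.135) = 0.554.

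| US sensitivity | US detection rate | Power, normal approximation | Power, Fisher exact |
|---|---|---|---|
| 25.6% (lowest in the protocol) | 2.05% | 92.7% | 91.9% |
| 35% (planning value) | 2.80% | 80.1% | 76.6% |
| 40% | 3.20% | 70.5% | 65.7% |
| 47% (pooled) | 3.76% | 55.4% | 49.5% |
| 62.5% (highest in the protocol) | 5.00% | 24.6% | 20.1% |

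The Fisher column comes from full enumeration of the two binomial counts at 382 per arm. The pooled-variance normal formula agrees with the unpooled one to within 0.4 percentage points.

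**Step 3. How small a shift matters.** At a US sensitivity of 38% (p = 3.04%) the normal-approximation power is 74.5%. Three percentage points of sensitivity therefore cost more than five points of power.

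**Step 4. Compare the sources.** The 35% is cited to references 12, 13 and 14. The warning about understated US performance is cited to 12, 14 and 24. The overlap is 12 and 14; reference 13 is not criticised anywhere in the article.

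**The case against.** The strongest case on the other side has five parts.

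- **The sources are only partly affected, and the size of any bias is unknown.** Reference 13 is not criticised, and the Introduction says only that US may have been underestimated (the Discussion is firmer). The article says 35% was estimated to reflect an observed range; it does not say that 35% is the value any one study reported. Since the prospective studies go down to 25.6%, 35% may already lie above some raw values. All of this stands. A reader might infer that the 80% holds only if the bias persists in the trial. The document does not support that, because it does not show how much bias, if any, remains in 35%.
- **The 47% is not shown to be the right value.** It is a pooled figure for US in cirrhosis. Nothing says that it comes from randomised, two-round or comparably high-risk cohorts, whereas the protocol states a reason for preferring prospective surveillance studies. This stands too. A reader might infer that the trial's true power is about 55%; that is one scenario within a range.
- **Only one input is moved.** If HBP-AMRI sensitivity were 94.5% alongside a US value of 47%, power would be 63%. This is a fair point, and the table is conditional on the other inputs.
- **A second look may add less to US than it seems.** A reader might model two looks for every tumour. If half of those missed at round 1 are still early at an independent second look, the cumulative sensitivities are 46% and 94.5% and power is 64%. But the 8% is cumulative, so tumours arising after round 1 get one look. If only half are present at round 1, the sensitivities become about 41% and 92% and power is 72%. Persistent body habitus and liver morphology also make the looks less than independent. The 64% therefore overstates the loss from this mechanism, and the conclusion does not rely on it.
- **The inputs are printed, recruitment began in August 2022, and power scenarios may sit in a fuller document.** This does not dispose of the point. The article itself prints an unconditional power figure together with evidence that bears on its main input, and how a null result will be read can still be settled while follow-up continues.

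**Conclusion.** The point holds as a matter of an unadjusted and possibly optimistic planning value. It is not an arithmetic error: 806 is correct for its inputs, and 35% lies inside the protocol's quoted range. What the document does not support is the unconditional 80%. Two of the three sources for the US rate fall under the protocol's own warning about understated US performance, and any such understatement overstates power.

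The result is sensitive to this input. Over the protocol's own US range, normal-approximation power runs from 93% to 25%, with 80% at 35%, 71% at 40% and 55% at 47%. With the planned Fisher exact test, power at the planning value itself is about 77%, falling to about 66% at 40% and 49% at 47%. These figures assume 382 evaluable per arm, 8% prevalence and 90% HBP-AMRI sensitivity. They do not say where in the range the true US sensitivity lies.

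**What to change.** Keep 806 participants, the endpoint and the test. Make three changes to the text:

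1. In Sample size, replace the single 80% claim with power across the protocol's own US range, computed for the planned Fisher exact test. For example: with 403 per arm and 5% dropout, power is about 92%, 77%, 66%, 49% and 20% if US sensitivity is 25.6%, 35%, 40%, 47% and 62.5%, with prevalence 8% and HBP-AMRI sensitivity 90%.
2. State that 35% comes partly from intraindividual studies that may understate US in a randomised two-round comparison.
3. State that a non-significant primary result will be read from the 95% confidence interval for the difference in detection rates, and not as evidence that the two modalities detect equally.

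The change is to wording only, with no added patients or procedures. The downside is that the stated power becomes less favourable.
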